**Fig. 2 Fig2:**
[figure not shown]
Proposed exercises illustration of each program of the VIVIFRAIL© multicomponent exercise methodology. Modified from Izquierdo and colleagues (2017)

The intervention will be discontinued due to any condition or adverse event that does not allow the performance of exercises with security or if requested by any participant. If necessary, one medical team will be disposable to offer assistance at any moment.

The participants will be instructed to does not enroll in other physical activity intervention during the period of 12 weeks of intervention.

After initial assessment and categorization, the multicomponent program will be carried out for 12 weeks, totaling 60 sessions. Two weekly supervisioned sessions will be held (60 min) with an interval of 1 day between them. Participants will receive all materials (elastic bands, towel and bottles with water/sand) to perform the exercises and will be trained to perform exercises individually at home 3 days weekly in order to complete 5 days per week. Instructions will be adapted to the focused population and will be provided in Portuguese. Adherence to the intervention will be monitored using a frequency control spreadsheet before the start of each session. Participants will be instructed to report possible adverse events.

Participants may withdraw from the study for any reason at any time. The investigator also may withdraw participants from the study in order to protect their safety and/or if they are unwilling or unable to comply with required study procedures. To promote participant retention and complete follow-up, all the participants will receive written feedback regarding the assessments performed.

### Outcomes

Primary and secondary outcomes will be accessed at baseline, after 12 weeks (end of intervention) and 24 weeks (Table 4).

**Table 4 Tab4:** Primary and secondary outcomes for the participants of the study

	Measurement	Baseline (T0)	Post 12 week of Intervention (T1)	12 weeks of follow-up (T2)
***Primary outcomes***	Plasma levels of inflammatory cytokines	x	x	x
	Function of leukocytes in the peripheral circulation	x	x	x
***Secondary outcomes***	Short Physical Performance Battery	x	x	x
	Maximal isometric handgrip strength (kg.f)	x	x	x
	Gait speed (m/s)	x	x	x
	Fatigue	x	x	x
	Geriatric depression Scale (GDS)	x	x	x
	Dual-task_gait + verbal_ (m/s)	x	x	x
	Quality of Life (EQ-5D)	x	x	x
	FRAIL-BR	x	x	x
	SARC-F	x	x	x
	Physical activity frequency during follow-up			x

#### Primary outcomes

The primary outcome measure is a change in the inflammatory profile after a 12-week multicomponent physical exercise program (VIVIFRAIL©), whether a reduction in inflammatory mediators in serum (IL-6, TNF- α, IL1beta, IL-17, IL-22, and CXCL-8) or culture supernatants (IL-6, TNF- α, IFN-gamma and IL-17) or an increased production of anti-inflammatory mediators (IL1RA and, IL-27) in serum or IL-10 and IL-4 in culture supernatants. We hypothesize that the intervention would lead to an anti-inflammatory profile.

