**Discussion:**

We expect a reduction in inflammatory interleukins or an increase in anti-inflammatory mediators in those who performed the VIVIFRAIL© protocol. The results of the study will imply in a better knowledge about the effect of a low-cost intervention that could be easily replicated in outpatient care for the prevention and treatment of frailty, especially regarding the inflammatory and anti-inflammatory pathways involved in its pathophysiology.

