Few controversial studies investigated the effect of exercise on inflammatory biomarkers in frailty. A stabilization of IL-6 and CRP was observed in frail and pre-frail older persons during physical training and nutritional support, while controls presented an increase in these cytokines [12]. Moreover, those who improved physical performance lowered IL-6 levels. In another study, a resistance training for knee flexors and extensors muscles did not influence low-grade inflammation in older adults. However, plasma levels of TNF type 1 receptors were inversely related to the muscle strength at the end of 12-weeks [13]. In youngers, the increase in the serum level of TNF-α after intervention correlated with reductions in muscle mass after a 4-week follow-up period, suggesting that TNF-α may play a role in muscle loss due to detraining [14]. Collectively, these studies show the potential anti-inflammatory role of physical activity.

Thus, this single-center parallel randomized controlled trial will allow to investigate whether a low-cost multicomponent exercise program called VIVIFRAIL© [15, 16] has benefits for reducing inflammation and improve the functional status among older persons with different frailty status. This program is performed according to the functional capacity and has been demonstrated to be a safe and effective to reverse the functional decline associated with acute hospitalization in seniors [17, 18]. The specific objectives of this RCT will be evaluate the effectiveness of the VIVIFRAIL© [15, 19] program with respect to the concentration of inflammatory and anti-inflammatory mediators and in the functional status of older persons in the different frailty status during 12-weeks. It is hypothesized that older persons submitted to the VIVIFRAIL© exercise protocol will present a decrease in serum levels of pro-inflammatory interleukins, associated with an increase in serum levels of anti-inflammatory interleukins and, secondarily, an improvement in the functional status is expected.

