#### Secondary outcomes

Secondary outcomes are a change in: (1) physical performance according to the SPPB, (2) handgrip strength, (3) fatigue according to specific items of the CES-D scale, (4) gait speed, (5) dual-task gait speed, (6) depressive symptoms, (8) FRAIL and SARC-F scores, and (7) quality of life.

We hypothesize that the intervention group could present at least a 1-point increase in the SPPB, better measurements of strength and gait speed, less referred fatigue and depressive symptoms, and better quality of life.

All the participants will be coded using numbers and the data will be stored electronically. After storage, data will be checked by a second researcher to ensure data quality*.* All participant information will be stored in areas with limited access. All records that contain names or other personal identifiers will be stored separately from study records identified by code number.

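### The primary outcome and hypotheses name no comparator, and the plan does not say that a between-arm test decides them, so a within-arm reading stays open

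*Protocol article*

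**What the plan says.** Primary outcomes defines the endpoint thus: "The primary outcome measure is a change in the inflammatory profile after a 12-week multicomponent physical exercise program". It then gives the direction, "whether a reduction in inflammatory mediators in serum" or in culture supernatants, or else higher anti-inflammatory mediators. The section closes with "We hypothesize that the intervention would lead to an anti-inflammatory profile". The control arm is not mentioned.

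The hypotheses follow the same pattern:
- Abstract, Discussion: "We expect a reduction in inflammatory interleukins or an increase in anti-inflammatory mediators in those who performed" the programme.
- Background: "older persons submitted to the VIVIFRAIL© exercise protocol will present a decrease in serum levels of pro-inflammatory interleukins".
- Secondary outcomes: "We hypothesize that the intervention group could present at least a 1-point increase in the SPPB".

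Other sections do bring in the control arm. Design and participants describes a parallel randomised comparison with usual health promotion. Control group links that arm, if awkwardly, to changes in serum biomarkers. Statistical analyses plans intention-to-treat analysis and a between-group Student t-test or Mann-Whitney test. It does not say whether that test uses 12-week values or changes, or that it decides the primary outcome. For differences between time points it plans a one-way repeated-measures ANOVA or Friedman test. The sample size rests on a 30% reduction in IL-6, with no statement of what the reduction is measured against.

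**The concern.** Only the exercise arm undergoes the programme, so a change after the programme reads literally as a change inside one arm. The listed test that matches that wording most closely is the repeated-measures one, which cannot compare arms. A reduction from baseline may come from retesting, season, assay drift or regression to the mean, and randomisation protects against these only when the arms are compared.

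The wording also sits badly with evidence the protocol cites in its favour. Background reports: "A stabilization of IL-6 and CRP was observed in frail and pre-frail older persons during physical training and nutritional support, while controls presented an increase". The effect there was a difference between arms without a fall in the trained arm. Read literally, the same result here would not be a reduction. At stake is whether the headline claim rests on the randomised contrast or on a before-after change.

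**Working it through.** **1. Does the sample size settle the comparator?** The inputs in Statistical analyses are a 30% reduction, 80% power, 5% error and 18 per group. No SD is given, so 18 cannot be reproduced directly. It can be solved backwards, taking the test as two-sided (an assumption), with 1.960 + 0.842 = 2.802.
- Two-arm comparison: standardised effect = 2.802 × √(2/18) = 0.934. The implied SD is 0.30/0.934 = 0.32 of the mean.
- One-arm paired comparison: the implied SD of change is 0.30 × √18/2.802 = 0.45 of the mean.

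Both readings give 18, so the figure does not show whether the 30% is against control or against baseline.

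**2. How much does the choice of test matter?** From the plan: 22 randomised per arm in each frailty state, 18 needed after dropout, three visits. Assumed, because the document gives none of these: normal data with SD 1 at each visit, equal correlation r = 0.6 between visits (range 0.4 to 0.8), and the shifts below, present at both follow-up visits. Tests are two-sided at 5%, with 20,000 simulated trials per setting.

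The standard error of the arm difference at n = 22 and r = 0.6 is:
- 12-week values: √(2/22) = 0.302
- change from baseline: √(4(1 − r)/22) = √(1.6/22) = 0.270
- baseline-adjusted: √(2(1 − r²)/22) = √(1.28/22) = 0.241

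Proportion of trials with a significant result, 22 per arm, r = 0.6:

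| Test | Exercise flat, controls +0.5 SD | Exercise flat, controls +0.8 SD | Both arms shift 0.4 SD |
|---|---|---|---|
| Within-arm repeated-measures ANOVA, exercise arm | 5% | 5% | 54% |
| Planned t-test, 12-week values | 37% | 73% | 5% |
| Planned t-test, change | 44% | 82% | 5% |
| Baseline-adjusted comparison | 51% | 89% | 5% |

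The within-arm 5% counts both directions and is chance alone.

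**3. Sensitivity.**
- With r from 0.4 to 0.8, the within-arm figure under a shared shift runs from 38% to 85%. The baseline-adjusted figures run from about 42% to 76% (+0.5 SD) and 79% to 99% (+0.8 SD).
- The t-test on 12-week values does not depend on r. The t-test on change runs from 32% to 73% and from 65% to 98%.
- At 18 per arm and r = 0.6, the shared-shift figure is about 45%, and the baseline-adjusted figures are about 43% and 82%.

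**The case against.** A reader might infer that the plan will count a shared drift as benefit and stabilisation as failure. The document does not support that. Primary outcomes says what is measured and which direction is expected; it does not say that a within-arm test decides the trial. A statement that an intervention leads to something is naturally read against control in a randomised trial. The design section names the comparison, and a between-group test is planned. On the figures above, that test stays near 5% when the arms do not differ, and it does detect stabilisation. The two errors arise only if that test is set aside.

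The stabilisation study is also a limited precedent. It combined training with nutritional support, and the next sentence of Background says that participants whose performance improved had lower IL-6. Expecting a fall is therefore reasonable and does not contradict the evidence. The reference for the 30% may be clear from the cited trial, which is not at hand, and the exact endpoint form is often left to an analysis plan.

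All of that stands, and it makes the consequence conditional. It does not remove the gap. The article itself fixes both the outcome definition and the list of tests. It gives the outcome no comparator, and it gives change over time a test with no group factor. Nothing in it says which test governs the primary claim.

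**Conclusion.** The point holds as a defect of definition with a conditional consequence. As worded, the plan leaves room for a within-arm claim of success in a trial designed to compare arms. If that room is used, a shared 0.4 SD shift would give a significant change in the exercise arm in about 54% of trials (38% to 85% over the assumed correlations), and the cited stabilisation pattern would be found only by chance. If the planned between-group test is used, neither problem arises. What is then lost is power: about 37% or 73% on 12-week values, against about 51% or 89% with baseline adjustment.

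These figures depend on an assumed correlation and assumed shifts. They show direction and rough size and do not predict what this trial will report. The correction should be made before analysis, because it determines what may be called a positive result.

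**What to change.** - **Primary outcomes:** define the outcome as the between-arm difference (or ratio, on the log scale) at 12 weeks, adjusted for the T0 value. Define benefit relative to control: lower for inflammatory and higher for anti-inflammatory mediators, whether the gap comes from a change with exercise or a change in controls. Align the abstract and the Background hypothesis.
- **Statistical analyses:** name that baseline-adjusted comparison as the analysis that decides the primary outcome. Label the repeated-measures ANOVA and Friedman tests descriptive. State whether the 30% reduction in IL-6 is relative to baseline or to control.
- **Secondary outcomes:** word the SPPB hypothesis as a 1-point difference from control.

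The cost is revised wording and a slightly different model, using data already scheduled at T0 and 12 weeks, with no extra participants or visits. The sponsor gives up one thing: improvement inside the exercise arm alone can no longer be reported as meeting the primary outcome.

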**Methods/design:**

This is a randomized clinical trial in an outpatient geriatrics clinic including older adults ≥60 years. For each frailty state (frail, pre-frail and robust), forty-four volunteers will be randomly allocated to the control group (*n* = 22) and the intervention group (*n* = 22) for 12 weeks. In the control group, participants will have meetings of health education while those in the intervention group will be part of a multicomponent exercise program (VIVIFRAIL©) performed five times a week (two times supervised and 3 times of home-based exercises). The primary outcome is a change in the inflammatory profile (a reduction in inflammatory interleukins [IL-6, TNF- α, IL1beta, IL-17, IL-22, CXCL-8, and IL-27] or an increase in anti-inflammatory mediators [IL-10, IL1RA, IL-4]). Secondary outcomes are change in physical performance using the Short Physical Performance Battery, handgrip strength, fatigue, gait speed, dual-task gait speed, depressive symptoms, FRAIL-BR and SARC-F scores, and quality of life at the 12-week period of intervention and after 3 months of follow-up.

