#### Inflammation

The peripheral blood of all participants will be collected. From everyone, approximately 9 mL of blood will be collected in tubes containing clot activator and 9 mL in tubes containing sodium heparin for peripheral blood mononuclear cells (PBMCs) and polymorphonuclear cells (PMNs) isolation. The serum will be separated after clot formation by centrifugation at 1200 *g* for 15 min at room temperature, then the serum will be collected, aliquoted and immediately stored at 20 °C. The cytokine measurement will be performed using ELISA with specific commercial kits for IL-6, TNF- α, IL1beta, IL-17, IL-22, CXCL-8, IL1RA, and IL-27 (R&D Systems and Biolegend manufacturers’ instructions).

PBMCs will be isolated using Ficoll-Hypaque density gradient centrifugation (density 1.077 - Pharmacia Biotech, Piscataway, NJ, USA). After removing PBMCs, the buff-coat cells (containing PMNs) will be collected and diluted in fresh RPMI medium and submitted to new centrifugation over a Ficoll-Hypaque solution at a density of 1.119). After separation, PBMCs and PMNs will be resuspended (2 × 10^6^ cells/mL) in RPMI medium supplemented with fetal bovine serum (10%), L-glutamine, sodium pyruvate and gentamicin (RPMI-S) and distributed in 24-well plates. Cultures will be maintained without additional stimulation or stimulated with ultrapure LPS (100 ng/mL - Invivogen) and PMA (100 ng/mL - Sigma) for PMNs and with ultrapure LPS (100 ng/mL - Invivogen) and PHA (10 mg/mL) for PBMCs. The cells will be kept for 24 h, at 37 °C in a CO_2_ incubator (5%). After the culture period, the supernatant will be collected and stored at − 80 °C and will be evaluated by ELISA with commercial kits for each cytokine (IL-10, IL-4, IFN-gamma, IL-17, TNF- α, IL-6) (R&D Systems and Biolegend).

The details of the pro-inflammatory and anti-inflammatory mediators investigated in this study are presented in the Table 2.

**Table 2 Tab2:** Pro-inflammatory and anti-inflammatory mediators

Mediator	Major Cellular Sources	Major Activities
**IFN-gamma**	Th1 cells, NK cells	Activation of inflammatory macrophages (M1), inhibition of Th2 responses, induction of leukocyte migration.
**IL-1beta**	Monocyte/macrophages, PMNs.	Synthesis of acute-phase proteins by hepatocytes, induction of local and systemic inflammatory effects.
**IL-1RA**	Monocyte/macrophages, dendritic cells.	Specific inhibitor of IL-1alpha and IL-1beta by competition with the cellular receptor.

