### Statistical analyses

First, sample calculation was based in a previously published results from a clinical trial of resistive physical intervention among frail older adults [31]. This study is similar to our design and outcomes. In this trial, outcomes involved inflammatory biomarkers. To date, VIVIFRAIL trials were done in inpatients and nursing home patients and without inflammatory biomarkers as outcome measurement. For a 30% reduction in IL-6 with 80% power and a 5% error, we would have 18 older adults in each group for 12 weeks. Assuming a drop out until 25% within this period, the groups should be composed of 22 elder adults each.

Statistical analyzes will be performed using the SPSS program (version 23.0; SPSS, Inc., USA) and R version 3.6.2. Initially, the Shapiro Wilk and Levene tests will be used to test the distribution and homogeneity of the data. Descriptive analysis will be performed and the means and standard deviation of the variables with normal distribution will be presented, and the median and maximum and minimum values ​​for the non-normal variables and 95% confidence intervals.

Analysis by intention to treat will be performed. A sensitivity analysis will be performed for missing data, through multiple imputation. To compare the variables between the groups, the Student t-test will be used or the Mann-Whitney test for non-parametric variables. To assess the difference between the moments of intervention, one-way analysis of variance (ANOVA-oneway) with repeated measures or the Friedman test for nonparametric variables will be used.

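### The primary outcome is an *or* list of 14 cytokine measures with no lead marker or success rule, while the stated error and power are for IL-6 alone

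*Protocol article*

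**What the plan says.** Under Primary outcomes, the Protocol article gives the routes to success as follows:

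- "a reduction in inflammatory mediators in serum (IL-6, TNF- α, IL1beta, IL-17, IL-22, and CXCL-8"), which is six markers;
- "or culture supernatants (IL-6, TNF- α, IFN-gamma and IL-17"), which is four;
- "or an increased production of anti-inflammatory mediators (IL1RA and, IL-27) in serum or IL-10 and IL-4 in culture supernatants", which is two plus two.

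Table 4 names the primary outcomes only by class: circulating cytokine levels and "Function of leukocytes in the peripheral circulation".

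Statistical analyses gives a single sizing basis, "For a 30% reduction in IL-6 with 80% power and a 5% error", leading to 18 per group and 22 after allowance for dropout. It does not call IL-6 primary or say whether serum or culture IL-6 is meant. Variables are then compared between groups by t-test or Mann-Whitney test.

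The abstract sets the stratum sizes: "For each frailty state (frail, pre-frail and robust), forty-four volunteers will be randomly allocated to the control group" or the intervention group, 22 in each. It lists IL-27 among the inflammatory interleukins whose reduction counts as benefit. Primary outcomes lists IL-27 among the anti-inflammatory mediators whose increase counts.

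**The concern.** An outcome that can be met by several alternative routes has a higher false-positive rate than any one route. Here the routes are joined by *or*, each variable gets its own test, and nothing says how many markers must move, or which. A report of one favourable cytokine out of 14 could therefore be presented as meeting the primary outcome. The 5% error in the sample-size paragraph would not describe that claim, because it was set for one marker.

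The IL-27 conflict makes this worse: with the two sections read together, a change in either direction could be counted as success.

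**Working it through.** **The plan's own figure.** The 18 per group cannot be recomputed because no standard deviation is given. Solved backwards with the normal approximation, two-sided 5% and 80% power:

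d = sqrt(2 × (1.960 + 0.842)² / 18) = 0.934

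A 30% reduction then implies an SD of about 30/0.934 = 32% of the mean. This one-marker calculation is the only place where the article attaches an error rate to anything.

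**Count of routes** (Primary outcomes): 6 + 4 + 2 + 2 = 14.

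**Reading A: one favourable marker suffices, one stratum, no true effect.** The article does not state sidedness. I assume two-sided 5% tests, so 2.5% in the favourable direction.

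- Independent markers: 1 − 0.975^14 = 29.8%.
- Equally correlated markers (simulation, t-tests, 18 per arm, 20,000 runs):

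| Assumed correlation | At least one favourable result |
|---|---|
| 0.3 | 22.6% |
| 0.5 | 18.1% |
| 0.7 | 12.5% |
| 0.9 | 7.4% |

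The documents give no correlations, so this is a range and not an estimate.

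**Reading B: only the four classes are alternatives**, each judged by one independent test at 2.5%: 1 − 0.975^4 = 9.6%.

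**If each of the three strata is tested separately** (14 × 3 = 42 tests under reading A):

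- Independent: 1 − 0.975^42 = 65.5%.
- At correlation 0.3, 0.5 and 0.7 within a stratum: 54%, 44% and 34%.

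**If culture conditions are counted separately.** The Inflammation section describes two cell types, with "Cultures will be maintained without additional stimulation or stimulated with ultrapure LPS" and a further agent. That gives 4 to 6 conditions, depending on whether the stimuli are combined. Tests per stratum: 8 serum + 6 culture × (4 to 6) = 32 to 44. If independent: 1 − 0.975^32 = 56% to 1 − 0.975^44 = 67%.

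**Cost of keeping all 14 with Bonferroni** (0.05/14 = 0.00357) at d = 0.934: 33 completers per arm instead of 18. With 18, power per marker falls from 80% to about 46%.

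**IL-6 alone, tested unadjusted in each of three strata:** 1 − 0.975^3 = 7.3% favourable; 1 − 0.95^3 = 14.3% in either direction.

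**The case against.** Several objections stand, and they limit the point.

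- **Error control.** A reader might infer that the trial has none. The article states none, but an analysis plan that is not shown may, and such a procedure is commonly left there. What the article itself fixes is the definition of the primary outcome.
- **What *or* joins.** Within each class the markers are linked by *and*; *or* separates the classes. Nothing says one marker is enough, so reading A is one interpretation and reading B is another. Requiring every marker in a class to change would be stricter still. That three rules with such different error rates all fit the text is itself the defect.
- **Strata and culture conditions.** A reader might take 32–44 as the true number of endpoints and multiply by three. The article never says that each condition is a separate success criterion, or that success in one stratum is success for the trial. Stratum sizes of 22 per arm suggest separate comparisons, but Randomization and blinding also gives totals of 66 per arm, and Statistical analyses refers only to comparison between groups.
- **A likely or near-certain false success.** For 14 markers in one stratum, the favourable-direction figures of about 12–30% do not support this. Chances above one half need strata or culture conditions counted separately, with weak or no correlation.
- **Background against Outcomes.** The Background expects that participants "will present a decrease in serum levels of pro-inflammatory interleukins, associated with an increase in serum levels of anti-inflammatory interleukins". One might call this a contradiction of the *or* definition. It is a scientific expectation, and it can be broader than the success criterion without conflicting with it.
- **Choice of IL-6.** Table 2 gives IL-6 mixed activity, so choosing it is partly a scientific decision, and a composite would also be possible. IL-6 is, however, the only marker for which the article claims power.

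**Conclusion.** The point holds as a badly fixed definition of the primary outcome. Fourteen marker and sample combinations are offered as alternatives without a lead marker, composite or decision rule, and the stated 5% error and 80% power cover one of them.

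If a single favourable marker suffices, the false-favourable rate within a stratum is about 12 times the nominal 2.5% with independent markers (29.8/2.5), and about 5 to 9 times at assumed correlations of 0.7 to 0.3. If only the four classes are alternatives, it is about 4 times. These figures rest on two-sided 5% tests and equal correlation, and the four-class figure on one independent test per class. The larger figures for three strata or separate culture conditions are conditional, because the article does not say that either is done.

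The opposite directions given for IL-27 are a plain inconsistency and depend on none of these assumptions.

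**What to change.** Before any outcome data are examined by arm:

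1. Name one primary endpoint: the between-arm difference in change in IL-6 from baseline to 12 weeks. State that it is serum IL-6 if that is what the sizing used, and align Table 4, which says plasma.
2. Move the other serum mediators and all culture-supernatant results to secondary or exploratory families, with Holm or false-discovery-rate control within each family.
3. State whether IL-6 is tested once across strata, in a stratified comparison, or in each stratum with the 5% shared across the three.
4. Reconcile the direction of IL-27 between the abstract and Primary outcomes.

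The cost is protocol and registry wording, with no new data. A result on another cytokine alone could no longer be called primary success. A single stratified test needs no more participants. Sharing the 5% equally over three strata does have a price: at d = 0.934 and 18 completers per arm, power per stratum is Φ(0.934 × sqrt(9) − 2.394) = Φ(0.408), about 66% instead of 80%. Restoring 80% would take about 18 × (3.236/2.802)² = 24 completers per arm. That choice should be made openly.
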